### Dissemination

The research will be summarized in a technical report to the funding agency, the UK National Institute for Health Research (NIHR). This report will be in the public domain. The findings of the research will be disseminated locally, regionally, and nationally to professional and user groups through established research and service networks (for example, the South London Stroke Research Group, the UK Stroke Forum and the UK Stroke Research Network). A summary of findings written in lay language will be posted to study participants who wish to be informed about the study outcome. We will seek publication in peer-reviewed journals and presentations at international scientific meetings to reach the wider healthcare community. To ensure that the validity and scientific value of the study can be adequately evaluated by consumers of research, study reporting will follow the CONSORT
[66,67] and CONSORT for nonpharmacologic interventions
[68] guidelines. All dissemination outputs from the study require approval from the funding agency (UK NIHR) before publication.

## Discussion

### Strengths

To our knowledge, the present study is the first to explore respiratory muscle strengthening as a means to improving cough effectiveness and protecting from pneumonia in acute stroke. Although little research has been conducted in this area to date, several studies of good methodologic quality provide a physiological rationale and demonstrate the potential for physiological improvement through RMT in stroke.

The current study applies a method of cough flow measurement that is detailed and physiologically accurate. This method compares favorably with the use of portable peak flow meters, which have been used in other clinical studies in spite of uncertainty over their accuracy in measuring cough flow.

### Weaknesses

The methods for identifying the presence of swallowing difficulty and pneumonia in the current study may be regarded as a limitation. To minimize participant burden created by additional medical procedures, it was decided to take a pragmatic approach and observe clinical and self-reported information on swallowing function and pneumonia. A more-detailed instrumental assessment of swallowing, such as video-fluoroscopic examination of swallow, could be used to determine the degree of dysphagia and aspiration. Objective diagnostic criteria for pneumonia, including assessments of chest radiographs and blood results
[69,70], could be used to support the detection of pneumonia.

A further limitation to the study is the lack of investigator blinding. The investigator is masked to treatment-allocation sequence, but is aware of group allocation from the point of randomization.

Although the clinical purpose of this research is to reduce the risk of pneumonia after stroke, the study uses voluntary cough flow as a surrogate primary outcome. This surrogate outcome was selected to minimize the required sample size. Designing the study according to the primary outcome, pneumonia, would require a considerably larger sample. For example, it could be assumed that both intervention groups would show a reduction in pneumonia rates from 15% to 7.5% compared with the control group. To give 80% power at the 5% significance level, this would require approximately 180 participants per group (using the χ^2^ test and not accounting for attrition).

The choice of voluntary cough flow as a surrogate primary outcome in this study was based on the physiological rationale to the research. Also, good evidence shows that reduced voluntary cough flow in stroke patients is associated with higher risk of aspiration, and therefore aspiration pneumonia
[35,36]. To our knowledge, the direct relation between voluntary cough flow and pneumonia has not been investigated in stroke populations. The importance of cough flow may be inferred from populations with neuromuscular conditions, where reduced levels of voluntary cough flow indicate the need for assisted airway clearance
[71]. The adequacy of voluntary cough flow as a surrogate measure for pneumonia will be assessed after the trial. It is likely that a proportion of study participants will develop pneumonia, and the association between voluntary cough flow and pneumonia will be assessed by using descriptive statistics or logistic regression analysis, as appropriate.

As described, the initial sample-size calculation was revised because of a higher-than-anticipated attrition rate. It is important to maximize participant retention in trials, to avoid conclusions that are biased through missing data
[72]. It is anticipated that the present pilot study will indicate strategies to minimize participant attrition and missing data. So far, provision of transportation for participants free of charge and the option to bring testing equipment to the participant’s location have greatly improved participant retention. Further strategies will be explored by reviewing reasons for discontinuing the study and considering alternative methods of data collection, in an effort to prevent missing data.

In conclusion, in trialing RMT in acute stroke, the present study investigates a novel approach for preventing poststroke pneumonia. Poststroke pneumonia presents a multifaceted clinical problem, and different strategies for reducing incidence rates are currently being researched. The current study will provide valuable information on the potential validity and feasibility of this particular approach.

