**Methods/design:**

Adults with moderate to severe stroke impairment (National Institutes of Health Stroke Scale (NIHSS) score 5 to 25 at the time of admission) are recruited within 2 weeks of stroke onset. Participants must be able to perform voluntary respiratory maneuvers. Excluded are patients with increased intracranial pressure, uncontrolled hypertension, neuromuscular conditions other than stroke, medical history of asthma or chronic obstructive pulmonary disease, and recent cardiac events. Participants are randomized to receive inspiratory, expiratory, or sham respiratory training over a 4-week period, by using commercially available threshold resistance devices. Participants and caregivers, but not study investigators, are blind to treatment allocation. All participants receive medical care and stroke rehabilitation according to the usual standard of care. The following assessments are conducted at baseline, 4 weeks, and 12 weeks: Voluntary and reflex cough flow measurements, forced spirometry, respiratory muscle strength tests, incidence of pneumonia, assessments of safety parameters, and self-reported activity of daily living. The primary outcome is peak expiratory cough flow of voluntary cough, a parameter indicating the effectiveness of cough. Secondary outcomes are incidence of pneumonia, peak expiratory cough flow of reflex cough, and maximum inspiratory and expiratory mouth pressures.

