### Study parameters

Additional file
1 gives an overview of the data collected at the respective time points. Peak expiratory cough flow (PECF) of voluntary cough at the end of the intervention period (day 29) is taken as the primary study outcome. This is in keeping with the clinical scenario of aspiration and resulting pneumonia. PECF is the parameter that indicates the speed of the air expelled from the lungs during the expulsion phase of cough. Voluntary cough PECF therefore reflects a person’s capacity to move aspirated particles from the lower airway back above the vocal cords and into the pharynx through a voluntary cough maneuver
[55]. Secondary study outcomes are incidence of pneumonia, maximum mouth pressures, and peak expiratory cough flow of reflex cough at day 29.

Participants’ age, height, and weight at the time of hospital admission are recorded from clinical records.

Swallow safety is determined from the clinical swallow assessment, conducted routinely for patients admitted with acute stroke. This entails a swallow screen administered by a trained nurse. The swallow screen is conducted according to a clinical algorithm and includes observation of alertness, oro-motor function, and swallowing function. If concerns are raised, the medical team and the speech and language therapist are alerted. A clinical swallow examination by a speech and language therapist is performed, and swallow-management strategies are implemented. In specific cases, an instrumental assessment of swallowing function is performed.

For the purpose of the present study, the swallow is deemed unsafe if any precautionary instructions are issued for the participant, such as nil by mouth, recommendations of modified food textures, or specific swallowing techniques. The swallow is deemed safe, if the participant is allowed to swallow normal fluids and a normal diet without any explicit precautionary instructions.

The presence of pneumonia is determined from clinical records, from communication with the medical team, and from the participant directly.

The Nottingham Extended ADL Scale
[56], a self-reported questionnaire, is used to assess participants’ functional independence in activities of daily living (ADLs).

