### Statistical analysis

Descriptive statistics will be used to present group characteristics at baseline; to compare study completers with participants who discontinued the study; and to compare participants with good training completion with those with poor training concordance. Training-safety data will be summarized descriptively and compared against pre-set safety parameters (standard safe ranges of vital parameters as used in clinical practice).

Inferential statistics will be used to evaluate the effect of treatment on the primary and secondary outcome parameters. The hypotheses under investigation are as follows: RMT (inspiratory or expiratory) is effective for improving voluntary cough effectiveness (voluntary cough PECF); RMT (inspiratory or expiratory) is effective for improving reflex cough effectiveness (reflex cough PECF); expiratory muscle training is effective for improving expiratory muscle strength (MEP); inspiratory muscle training is effective for improving inspiratory muscle strength (MIP); RMT (inspiratory or expiratory) is effective for reducing the incidence of pneumonia.

The sample-size calculation followed an ANOVA model of inferential statistical analysis. However, it is anticipated that the study sample will show considerable heterogeneity, in which case, an analysis of covariance (ANCOVA) model is more powerful in detecting a difference in study arms
[62]. ANCOVA will be used to compare group means of voluntary and reflex cough PECF, MEP, and MIP at the primary end point (day 29). The following covariates will be adjusted for: gender, age, smoking, stroke severity (NIHSS score), training intensity, and a predictor variable for “missingness”, which will be determined through logistic regression. Fisher Exact test will be used to compare the incidence of pneumonia from baseline through week 4 between the three study groups. Adjustments for multiple testing will be made by using the Benjamini-Hochberg method
[63].

Four approaches to dealing with missing values will be compared in a sensitivity analysis: intention-to-treat analysis, substituting missing values through predictive model-based imputation
[64]; intention-to-treat analysis, substituting missing values through propensity score imputation
[65]; intention-to-treat analysis, substituting missing values with baseline data; and complete case analysis, using only data from participants who completed the primary end point.

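### The article says it will assess cough flow as a surrogate for pneumonia, but the patient-level association it plans can show prognosis only

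*Protocol article*

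**What the plan says.** The protocol article, Discussion, Weaknesses, states that "the study uses voluntary cough flow as a surrogate primary outcome". It gives the reason: a trial designed on pneumonia would need a much larger sample. It adds that, to the authors' knowledge, the direct link between cough flow and pneumonia has not been studied in stroke. It then makes a commitment: "The adequacy of voluntary cough flow as a surrogate measure for pneumonia will be assessed after the trial". The means follow in the next sentence: "the association between voluntary cough flow and pneumonia will be assessed by using descriptive statistics or logistic regression analysis, as appropriate". That passage names no other method, no time point for either variable and no treatment term.

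Three other places bear on timing:
- Study parameters: "Peak expiratory cough flow (PECF) of voluntary cough at the end of the intervention period (day 29) is taken as the primary study outcome".
- Statistical analysis: "Fisher Exact test will be used to compare the incidence of pneumonia from baseline through week 4 between the three study groups".
- Abstract, Methods/design: "The following assessments are conducted at baseline, 4 weeks, and 12 weeks". The list that follows includes both cough flow and pneumonia.

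**The concern.** A surrogate end point is adequate when the effect of treatment on it predicts or captures the effect of treatment on the clinical outcome. An association across patients does not speak to that. Cough flow and pneumonia may move together because both follow stroke severity, while training raises cough flow and leaves pneumonia unchanged. A regression of pneumonia on cough flow would look the same in either case.

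The aims section says the pilot is to inform the value and design of a larger trial. A report that cough flow was found adequate could be read there as support for using it as the end point, and this analysis could not supply that support.

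Time order matters as well. If cough flow is measured after the pneumonia it is meant to explain, a recent pneumonia may itself have weakened the cough. Patients who died or withdrew after pneumonia would have no later cough measurement.

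**Working it through.** The article states no figure for this analysis, so there is none to reproduce. The check covers what the method can show, how many events to expect, and timing.

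**1. Claim against method.** The claim is adequacy as a surrogate. The method is association. Judging surrogacy would at least require relating the training effect on cough flow to the training effect on pneumonia, and the passage does not mention this.

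**2. Expected events.** Cases = participants × rate. Sample size section: 20 completers per group (60) and at most 90 recruited.
- Article's own example in Weaknesses (15% / 7.5% / 7.5%): 20 × 0.15 + 40 × 0.075 = 3 + 3 = 6; for 90, 30 × 0.15 + 60 × 0.075 = 4.5 + 4.5 = 9.
- National audit rates in Background (13 to 16%): 60 × 0.13 = 7.8, up to 90 × 0.16 = 14.4.
- Median for acute, general and rehabilitation units in Background (7.4%): 60 × 0.074 = 4.4; 90 × 0.074 = 6.7.

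**3. Power for a training effect on pneumonia**, without which surrogacy cannot be examined. Rates 15% v 7.5%, two-sided 5%. Normal approximation: z = [|p1 − p2| − 1.96 √(p̄q̄(1/n1 + 1/n2))] / √(p1q1/n1 + p2q2/n2).
- 20 v 20: (0.075 − 1.96 × 0.0999) / 0.0992 = −1.22, power 11%.
- 20 v 40 (training arms combined): (0.075 − 1.96 × 0.0822) / 0.0901 = −0.96, power 17%.
- Two-group exact Fisher test: 4% and 14%.
- At 90 recruited, normal approximation: 15% (30 v 30) and 22% (30 v 60).

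The article itself puts a pneumonia design at about 180 per group. Direct calculation gives more (232 with a three-group chi-square test, 278 for a pairwise comparison), but this point does not depend on that figure: 20 to 30 per group is far below any of them.

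**4. Power for the association alone.** Simulated score test, overall rate 10%, odds ratios assumed per SD of cough flow:

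| Odds ratio | N = 60 | N = 90 |
|---|---|---|
| 1.5 | 14% | 22% |
| 2 | 33% | 47% |
| 3 | 61% | 80% |

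Even the prognostic question will be answered imprecisely.

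**5. Timing, if the defined outcomes are paired.** Cough flow is taken at day 29 and the pneumonia window closes at week 4. Every case in the window then precedes the cough measurement or at best coincides with it. The following illustration is not based on trial data. Assumptions: SD 150 L/min, training raises cough flow by 100 L/min, pneumonia is 10% in every arm (so training has no effect on it), and everyone has a day-29 value.

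| Assumed fall in day-29 cough flow after pneumonia (L/min) | Significant association, N = 60 | N = 90 |
|---|---|---|
| 0 | 4% | 5% |
| 100 | 30% | 42% |
| 150 | 56% | 74% |

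The documents give no figure for such a fall. The table shows only that reverse causation could produce an association where no surrogacy exists.

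**The case against.** The strongest reply is that the timing problem is not in the text. The Weaknesses passage names no time points. Cough flow and pneumonia are both recorded at baseline, 4 and 12 weeks, so correctly ordered pairs are available and nothing excludes them. A reader might infer that the plan will regress pneumonia through week 4 on day-29 cough flow, because the surrogate is called the primary outcome and that outcome is fixed at day 29. The documents do not say so. An article may also leave time points to a fuller plan. This reply stands: reverse causation is a conditional risk, and the simulated rates depend on an assumed fall in cough flow.

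It can also be said that the sentence is a remark in the Discussion of a pilot, outside the listed hypotheses, with no decision rule for calling the surrogate adequate. The article is candid that the relation is unproven, and its wording allows plain description if events are few. All of this is true and limits the weight of the point. A reader might infer that a finding of adequacy will settle the larger trial's end point, but the article does not say this.

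The audit rates may also not carry over to participants who enter up to two weeks after onset and must be able to consent and perform the manoeuvres. The 6 to 9 cases from the article's own example are therefore the safer range.

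The mismatch between claim and method survives these replies. Choosing time points in a fuller plan would not turn an association into evidence of surrogacy.

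**Conclusion.** The point holds in limited form. As written, the article promises to assess surrogate adequacy by a method that can show only prognosis. With about 6 to 9 pneumonia cases under its own example, or about 8 to 14 at the audit rates, the trial also cannot test whether cough flow carries the treatment effect: power for the pneumonia effect itself is 11 to 17% at 20 per group by normal approximation. These figures assume 60 to 90 participants and the rates quoted in the article.

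Reversed time order is a risk only if day-29 cough flow is paired with pneumonia through week 4. The article neither specifies that pairing nor rules it out. The primary and secondary analyses are unaffected.

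**What to change.** - Replace the statement that surrogate adequacy will be assessed with an exploratory, prognostic association between cough flow and pneumonia, reported with its confidence interval.
- Make baseline cough flow against subsequent pneumonia the main pairing, in all randomised participants with a baseline measurement.
- Relate day-29 cough flow only to pneumonia after day 29, in those with a day-29 measurement. State that this subset is selected (attrition was 32% at the sample-size review) and will have few events. Extending this pairing to everyone randomised is not workable without imputing the missing cough flows.
- Say that surrogacy is left to a larger study.

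The cost is wording only, since the abstract lists both measurements at baseline, 4 and 12 weeks. The downside is that the pilot can draw no conclusion about surrogacy, and the day-29 pairing will be imprecise.

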## Trial status

Recruitment to the study started in March 2011 and is expected to be complete by April 2014.

## Abbreviations

ACE: angiotensin converting enzyme; ADL: Activity of daily living; ANCOVA: analysis of covariance; ANOVA: analysis of variance; COPD: chronic obstructive pulmonary disease; CT: computed tomography; FEV: forced expiratory volume; FEV1: forced expiratory volume in 1 second; ID: internal diameter; IMT: inspiratory muscle trainer; MEP: maximum expiratory mouth pressure; MIP: maximum inspiratory mouth pressure; NHS: National Health Service; NIHR: National Institute for Health Research; NIHSS: National Institutes of Health Stroke Scale; NRES: National Research Ethics Service; PECF: peak expiratory cough flow; PEF: peak expiratory flow; PEP: positive expiratory pressure; PICF: peak inspiratory cough flow; RMT: respiratory muscle training; SD: standard deviation; UK: United Ki ngdom; USA: United States of America; VE: volume expired; VI: volume inspired.
